#### Outcomes and participant timeline

2.2.3.

First, during the enrolment assessment, a standardized neurological clinical interview for Parkinson’s Disease (Supplementary material 4) will be performed. This interview includes questions related to habits, disease start, education, and working life. At the same time, weight, height, and body mass index will be measured with a wall stadiometer and a TANITA SC-240MA scale. The length of the lower limbs will also be measured during standing position with a tape measure from the anterior superior iliac spine and the medial malleolus. Asymmetries between the lower extremities greater than 1 cm will be considered within the first exclusion criteria (comorbidities that affect balance or gait). As mentioned above, each phase of the study has three evaluation moments: baseline (T0), post-8-week-training (T1), and follow-up (T2) at 8 weeks after the physiotherapy programs have finished. Assessments will be performed by a different physiotherapist from recruitment and treatment besides a neuropsychologist, both blinded to the treatment assignment. The participants will be evaluated in an ON-medication state (1 h after the dopaminergic dose) on the schedule described in Figure 1. In each measurement session, the severity of the disease (Hoehn and Yahr, 1967; Fahn et al., 1987), cognitive and mental status (Hamilton, 1959, 1960; Mahieux et al., 1995; Dubois et al., 2000; Marinus et al., 2003), perception on quality of life (Peto et al., 1995; Powell and Myers, 1995; Sandín et al., 2020), and balance and gait performance will be registered through clinical tests (Tinetti, 1986; Giladi et al., 2000; Kegelmeyer et al., 2007; Franchignoni et al., 2010) as well biomechanics instruments. Table 2 shows the scales and clinical tests that will be used to evaluate the participants. For balance biomechanics, assessment will be used a dynamometric platform (Dinascan/IBV Biomechanics Institute of Valencia, Valencia, Spain) and the NedSVE®/IBV software (version 5.3.0.1, Biomechanics Institute of Valencia, Valencia, Spain). Balance will be assessed through the Romberg tests under four static conditions with increasing difficulty (see Figures 2A,B): (i) eyes open; (ii) eyes closed; (iii) eyes open on a foam rubber; and (iv) eyes closed eyes on the foam rubber (thickness of 9 cm, 56.7 kg/m3 of density, and resistance of 25%) (Escamilla-Martínez et al., 2021). Participants were asked to find the most stable position while barefoot with their arms relaxed on either side of the body, with their heels together and toes apart at a 30° angle. Additionally, four static functional balance tests will be assessed, using the Romberg test protocol with their eyes open: (i) to see the time on an analogy clock (visual); (ii) to answer a simple question (verbal); (iii) to pour the contents of one glass into another (lower motor); and (iv) to simulate comb the hair (upper motor). The instructions for each task were standardized to ensure uniform execution of the gesture. Participants will be asked to remain as still as possible with their heads in a neutral position and their gaze forward, except for the lower motor test where they will be allowed to observe their hands. Each test will last for 30 s and will be recorded two times. Finally, dynamic balance will be assessed with stability limits and rhythmic weight shift tests on the platform (Balaguer García et al., 2012). In the stability limits test, participants from the Romberg position will have to move a cursor (which reflected the position of their CoP) toward eight targets (front, front-right, right, rear-right, rear, rear-left, left, and front left) visualized on a computer monitor placed in front at their eye level. Once the target is reached, the subject will have to maintain the posture with the CoP displaced at the limit of stability until the end of the 8 s of each test (Balaguer García et al., 2012). On the other hand, in the rhythmic weight shifts tests, subjects will have to move their CoP to the direction and velocity of a moving target visualized on the computer monitor (Balaguer García et al., 2012). Each dynamic test will be registered two times. As a result, the primary outcome of the study will be the CoP sway area, which is defined as the surface over which the CoP moves during the measurement and is a valid indicator of detecting postural control changes in dual-task conditions (Campolettano et al., 2020; Morenilla et al., 2020). The secondary outcomes are shown in Table 2 and consist of biomechanics and clinical variables related to static and dynamic balance.

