#### Sample size and recruitment

2.2.4.

The software G*Power v.3.1 (Faul et al., 2007) has been used to determine the necessary sample size to detect a change in the primary outcome CoP sway area and differences between the groups (EG, PCG, ACG), with a small-medium effect (*f* = 0.15), a statistical significance of 5% at the two-tailed level, and a power of 95%. As a result of the above, 93 people diagnosed with PD will be recruited. If 20% of possible dropouts are also considered during the study, the initial recruitment should be 112 people. The sampling process will consist in the consecutive non-probabilistic method, in which the selection of individuals is carried out based on the fulfillment of participation criteria. The recruitment of participants began on 1 July 2021 and we estimate its completion on 31 July 2023. The participant recruitment procedure consists of three steps. First, the neurorehabilitation center has selected the possible candidates for the study based on personal and clinical characteristics, asks them by email the authorization to send information about the study, and contacted them using their telephone number. Then, the principal investigators called potential candidates to resolve possible doubts and confirm their participation. Finally, a physiotherapist will assess the selection criteria for all the volunteers and will provide informed consent for their signatures. The recruitment process will be repeated to complete the number of participants estimated for the study, extending participation to a new clinical center or public hospital if necessary.

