### Data collection, management, and statistical analysis

2.4.

Both evaluators (physiotherapist and neuropsychologist) will be responsible for exporting and filling in a database with variables from the scales and tests mentioned in Table 2 according to the code assigned to each patient to ensure his or her anonymity. To protect confidentiality during the study, the personal information of participants will be located separately from the main dataset on a local computer. The raw dataset will be maintained for 10 years after the completion of the trial with indefinite restricted access due to sensitive data. After the publication of the results trial, a fully anonymized patient-level dataset will be made publicly available on the registration trial website (clinicaltrials.gov). For participation in this study, no participant will receive any kind of incentives or compensation.

All analyses will be evaluated by intention-to-treat principles in terms of assignment to treatment and used a level of significance of 0.05. There are no interim analyses planned for this study. We will use the statistical software SPSS Statistics version 24.0 (IBM Corporation) for all the statistical analyses. Categorical variables were presented using frequency and percentage, and continuous variables as mean with standard deviation if they follow a normal distribution. To test for possible carryover effects of the experimental group, the sum of the values measured in the two periods for each subject will be calculated and compared across the two randomized groups (EG and PCG) using a test for independent samples (Serrao et al., 2019). There should be no difference if there is no sequence (balanceHOME program—usual daily activity or usual daily activity—balanceHOME program) effect.

To answer to the main aim of the study, a two-factor mixed multivariate analysis of variance (MANOVA) test was conducted to analyze the effects of within-subject factors (assessment times) and the between-subject factor (group) on the outcomes registered. The Bonferroni adjustment was used for *post-hoc* comparisons, and differences were declared statistically significant if the value of *p* was less than 0.05. Differences between groups for demographic outcomes were verified with a univariate analysis of variance (ANOVA) between-subjects test. Furthermore, to test for sex differences between groups, a chi-square analysis was used (San Martín Valenzuela et al., 2020b).

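### For the randomised EG versus PCG comparison, the time-by-group MANOVA uses T0 sway area as an outcome level rather than a covariate: valid, but less precise than T0 adjustment

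*Protocol article*

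**What the plan says.** Section 2.4 names the model for the main aim: a two-factor mixed MANOVA "to analyze the effects of within-subject factors (assessment times) and the between-subject factor (group) on the outcomes registered", with Bonferroni-adjusted post-hoc comparisons. It names no covariate. It also does not say whether the group main effect or the time-by-group interaction is the test of treatment.

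Section 2.2.3 defines the assessment times: "each phase of the study has three evaluation moments: baseline (T0), post-8-week-training (T1), and follow-up (T2". Baseline is thus one of the levels of the repeated factor. The same section makes centre-of-pressure sway area the primary outcome.

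Sections 2.1 and 2.3 place random allocation after the T0 assessment, 1:1 between EG and PCG only. T0 Hoehn and Yahr stage and Mini-Mental Parkinson score are used for stratification and matching; T0 sway area is not. ACG consists of people who already attend the group programme and is not randomised.

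Section 2.2.4 sizes the trial for three groups at f = 0.15 with "a statistical significance of 5% at the two-tailed level, and a power of 95"%, and concludes that "93 people diagnosed with PD will be recruited". It states neither the number of repeated measurements nor the correlation between them.

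**The concern.** Allocation follows T0, so treatment cannot separate EG from PCG at that visit. Entering T0 as a level of the outcome has two consequences for this pair.

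- The time-by-group test becomes a test on within-person changes from T0. Subtracting the whole of T0 removes too much whenever rho is below 1. The contrast then has a larger variance than the T0-adjusted one. A chance T0 difference of d also shifts the change-score estimate by −(1−rho)·d, and sway area is not among the factors balanced at randomisation.
- A group main effect averaged over T0, T1 and T2 includes a visit at which the treatment effect is zero.

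At stake is precision in the only randomised comparison, which has about 62 completers if 93 complete in total. T0 is already measured in everyone, so the precision costs nothing to collect.

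**Working it through.** **Inputs.** From the article: alpha 5% two-sided, planned power 95%, f = 0.15, three groups, N = 93 before dropout (section 2.2.4); two-thirds of participants randomised (abstract, Methods), 1:1 (section 2.3). Hence 93 × 2/3 = 62, or 31 per arm. Assumed, because the article does not give it: rho, taken from 0.3 to 0.9, with equal variances at all visits.

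**The plan's own figure.** For a repeated-measures interaction F test with k groups and m measurements, the noncentrality is f²·N·m/(1−rho), with (k−1)(m−1) and (N−k)(m−1) degrees of freedom. With k = 3, m = 6 and rho = 0.5, N = 93 gives 95% power. With m = 3 and rho = 0.5, 93 gives 81% and 95% needs 141; with m = 3, 93 reaches 95% only at rho of about 0.67. So 93 can be reproduced, but only with inputs that the article does not state. It does not settle what rho the authors had in mind.

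**Variance at T1, EG minus PCG** (outcome SD = 1, n per arm):

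- Change from T0: 2(1−rho) × 2/n
- Adjusted for T0: (1−rho²) × 2/n
- Ratio adjusted/change: (1−rho²) / [2(1−rho)] = (1+rho)/2

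**Power at T1, n = 31 per arm.** On 60 degrees of freedom, 80% power corresponds to a noncentrality of 2.847. The change-score effect with that power is 2.847 × √[4(1−rho)/31]. T0 adjustment divides the standard error by √[2/(1+rho)], so the noncentrality becomes 2.847/√[(1+rho)/2].

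| Assumed rho | Variance ratio | SE smaller by | Extra participants a change score needs, 2/(1+rho) − 1 | Effect with 80% power as change score (SD) | Noncentrality after adjustment | Power after adjustment |
|---|---|---|---|---|---|---|
| 0.3 | 0.65 | 19% | 54% | 0.86 | 3.53 | about 93% |
| 0.5 | 0.75 | 13% | 33% | 0.72 | 3.29 | about 90% |
| 0.7 | 0.85 | 8% | 18% | 0.56 | 3.09 | about 86% |
| 0.9 | 0.95 | 3% | 5% | 0.32 | 2.92 | about 82% |

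**Like-for-like check on the joint test of T1 and T2.** Simulation with 31 per arm, equal correlation across visits and an assumed 0.5 SD effect at both visits. Power of the multivariate time-by-group test, then of the same two-visit test adjusted for T0:

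- rho 0.5: 50% to 66%
- rho 0.7: 72% to 82%
- rho 0.9: 99.8% to 99.8%

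With no effect, the change-type and T0-adjusted tests all rejected between 4.4% and 5.1% of the time. Both approaches are valid for the randomised pair.

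**The non-randomised group.** Suppose two groups differ by a stable 0.5 SD at T0 and treatment does nothing. The adjusted difference is then expected to be (1−rho) × 0.5, that is 0.25, 0.15 and 0.05 SD at rho 0.5, 0.7 and 0.9. In simulation the T0-adjusted joint test rejected 20%, 13% and 7% of the time; the time-by-group test stayed near 5%.

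**The case against.** **The MANOVA also serves ACG.** The hypothesis in the Introduction sets home training against the traditional physiotherapy group, which is not randomised. A change-type test is defensible there, and the last calculation shows that T0 adjustment can mislead. This stands. A reader might infer that adding T0 as a covariate would improve the whole three-group analysis at no cost; the documents support that only for EG versus PCG.

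**The gain rests on an unstated rho.** This stands. Near 0.9 there is almost nothing to win.

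**T0 is not ignored.** The time-by-group contrast already uses it through within-person change. This stands: the issue is inefficient use. A reader might infer a much larger loss by comparing unlike tests. In an assumed case (0.6 SD at T1, half kept at T2, rho 0.5), the joint time-by-group test has about 53% power and the T0-adjusted T1 contrast about 76%. Much of that gap comes from moving to a single T1 contrast. Like for like, adjustment takes the joint test from 53% to about 67%, or the T1 contrast from about 64% to 76%. The group main effect would do far worse, but section 2.4 does not say that it is the treatment test.

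**The trial is a crossover.** The figures above cover phase 1 as parallel groups. In the same assumed case, with no carryover and the same correlation across phases, a within-person T1 comparison in 62 completers has variance 2(1−0.5) = 1 and noncentrality 0.6 × √62 = 4.7, hence over 99% power. This stands as a limit on the size of the gain and a reason not to discard second-phase data. Section 2.4 does not say how those data enter the MANOVA.

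**A condensed article leaves covariates to the analysis plan.** This carries less weight, because section 2.4 does state the model and its two factors.

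**Conclusion.** The point holds for EG versus PCG as a matter of efficiency. The stated model is valid but gives up precision that T0 adjustment would recover. In phase 1, at about 31 per arm, the T1 variance falls by 35%, 25%, 15% or 5% for rho of 0.3, 0.5, 0.7 or 0.9, and 80% power rises to about 93%, 90%, 86% or 82%. These figures assume equal variances, 93 completers split equally over three groups, and a rho that the article does not report.

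A reader might infer that the MANOVA is biased or has the wrong error rate; for the randomised pair it does not. Nor do the documents support adjusting the EG versus ACG comparison for T0 alone. The change is worth making because it is cheap, not because the planned test fails.

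**What to change.** - **EG versus PCG.** Model sway area at T1 and T2 with T0 sway area in the same test condition as covariate, its interaction with visit, and terms for visit, group and group-by-visit. Section 2.2.3 records eight static conditions (four Romberg, four functional) without naming one for the primary outcome, so the condition has to be named before the covariate is defined.
- **Reading the effect.** Take it from the EG minus PCG difference at T1 (and at T2), not from a group main effect that includes T0.
- **Second-phase data.** Where they are used, add period and that period's own T0, allow for repeated measurements on the same person, and keep the crossover data in the analysis.
- **EG versus ACG.** Keep this as a separate, non-randomised analysis. Show the change-from-T0 and T0-adjusted estimates together and comment if they disagree.

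The cost is a change of analysis wording and one degree of freedom per visit. T0 is already measured in everyone and the planned software fits the model. The change should be fixed before outcome data are examined by group.

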
**Table 2 tab2:** Summary of outcomes, measurement instruments, and assessment times.

Domain / Outcomes	Measurement instrument	Study period			
		Enroll (−t1)	Basal (t0)	Post (t1)	Follow (t2)
Enrollment					
Eligibility screen	Participation criteria	x			
Informed consent	Supplementary material 3	x			
Personal information	SNCI for PD (Supplementary material 4)				
Habits and working life					
Anthropometric data (weigh, height, body mass index, and lower limb length)	Wall stadiometer, TANITA SC-240MA scale, and tape measure	x			
Parkinson’s disease information					
Disease start and initial sign	SNCI for PD	x			
Parkinson’s disease severity	H&Y; UPDRS-III	–	x	x	x
Cognitive and mental status					
General cognitive state	MMP; SCOPA-COG	–	x	x	x
Executive cognitive function	FAB	–	x	x	x
Anxiety	HS for anxiety				
Depression	HS for depression	–	x	x	x
Balance and gait clinical performance					
Balance	MBT; TMT balance	–	x	x	x
Gait	TMT gait	–	x	x	x
Freezing of gait	FOG-Q	–	x	x	x
Quality of life					
Impact on life due COVID pandemic	CPI-Q		x	–	–
Perception of QoL due to Parkinson’s disease	PDQ-39		x	x	x
Confidence on self-balance	ABC scale				
Balance biomechanical performance					
*Static balance: Romberg and Functional test*					
ML and AP OP displacement (mm)	Dynamometric platform	–	x	x	x
Total CoP displacement (mm)		–	x	x	x
CoP displacement angle (°)		–	x	x	x
Mean CoP velocity (ms^−1^)		–	x	x	x
ML and AP CoP dispersion (mm)		–	x	x	x
CoP swept area (mm^2^)		–	x	x	x
*Dynamic balance: stability limits test*					
Reaction time (*s*)	Dynamometric platform	–	x	x	x
Maximum CoP displacement (%)		–	x	x	x
Success (%)		–	x	x	x
Directional control (%)		–	x	x	x
*Dynamic balance: rhythmic and directional control test*					
Directional adjustment (%)	Dynamometric platform	–	x	x	x
Perpendicular adjustment (%)		–	x	x	x
Gait biomechanical performance					
Speed (ms^−1^) and speed variability	3D photogrammetry Dynamometric platform	–	x	x	x
Stride length (m) and time (*s)*		–	x	x	x
Step length (m) and width (*m*)		–	x	x	x
Cadence (steps/min)		–	x	x	x
Double support time (%)		–	x	x	x
Stance and swing phase time (*s*)		–	x	x	x
Maximum ankle dorsiflexion during swing (°)		–	x	x	x
Maximum knee flexion during swing (°)		–	x	x	x
Maximum hip extension during stance (°)		–	x	x	x
Maximum hip flexion during swing (°)		–	x	x	x
Range of motion of lower limb joint (°)		–	x	x	x
CoP medial-lateral displacement (mm)		–	x	x	x
Mediolateral force amplitude (*N*)		–	x	x	x

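### The main-aim MANOVA on all registered outcomes does not carry the 95% power planned for CoP sway area, and on several counts of its outcomes it cannot be run

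*Protocol article*

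**What the plan says.** - **Primary outcome (section 2.2.3):** "the primary outcome of the study will be the CoP sway area".
- **Sample size (section 2.2.4):** the calculation is for that outcome and for differences among the three groups, with f = 0.15, 5% significance and 95% power. It concludes that "93 people diagnosed with PD will be recruited", and then: "If 20% of possible dropouts are also considered during the study, the initial recruitment should be 112 people".
- **Main analysis (section 2.4):** the main aim is answered by a two-factor mixed MANOVA of "within-subject factors (assessment times) and the between-subject factor (group) on the outcomes registered", followed by Bonferroni-adjusted post-hoc comparisons. No subset of outcomes, split by domain or separate model for sway area is named.
- **Outcomes (section 2.2.3 and Table 2):** clinical scales, static and dynamic balance variables and gait variables are measured at T0, T1 and T2. The static variables are recorded in four Romberg and four functional conditions. The gait rows include "Stride length (m) and time" and "Stance and swing phase time".

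**The concern.** A sample size justified on one variable supports a test of that variable. A multivariate test spreads its sensitivity over every contrast it contains. It also needs an error matrix of full rank, so the number of contrasts cannot exceed the error degrees of freedom. Table 2 is long relative to 93 participants.

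If the named test will not run, or runs but hardly responds to sway area, the analysts must choose which variables to drop or which conditions to merge once data are in hand. That freedom would then sit inside the main analysis. The issue is rank and power; it is separate from multiplicity and from which test condition is primary.

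**Working it through.** **1. The plan's own figure.** For a within-between interaction, λ = f²·N·m/(1−ρ), with df1 = (k−1)(m−1) and df2 = (N−k)(m−1). The number of measurements m and the correlation ρ are not stated, so they are assumptions here.
- k = 3, m = 3, ρ = 0.5: λ = 0.0225 × 93 × 3/0.5 = 12.6, power 0.81.
- k = 3, m = 6, ρ = 0.5: λ = 0.0225 × 93 × 6/0.5 = 25.1, power 0.952. This setting reproduces 93.
- Recruitment: 93 × 1.2 = 111.6, hence 112.

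Either way, the figure belongs to a univariate test of one outcome.

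**2. Outcome count from Table 2.** The items measured only once are left out, range of motion is counted once, and the swept-area row is taken to be sway area.
- 13 clinical scales + 8 static + 4 stability-limit + 2 rhythmic + 17 gait = 44.
- Static variables in eight conditions: 13 + 8 × 8 + 6 + 17 = 100.

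**3. Contrasts against error df.** Three visits give two time contrasts per outcome. Error df = N − 3 = 90 at N = 93, and 109 if all 112 complete.

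| Outcomes in the model | Contrasts | Against 90 |
|---|---|---|
| 8 static, one condition | 16 | computable |
| 44, one value each | 88 | just computable |
| 46 (range of motion at three joints) | 92 | singular |
| 64 (static block, eight conditions) | 128 | singular |
| 100 (all, static in eight conditions) | 200 | singular |

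The 128 and 200 counts also exceed 109. The 88-contrast version needs N − 3 ≥ 88, so at least 91 participants with complete data.

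**4. Linear dependency.** Stance time plus swing time equals stride time when all three come from the same strides. In that case any MANOVA containing all three is singular at every sample size.

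**5. Power, sway area only.** For three groups and q contrasts, Wilks' Λ gives F = [(1−√Λ)/√Λ]·(v/q), with v = N − q − 2 and df 2q and 2v. At q = 88, v = 3, so the denominator has 6 df. At q = 2, v = 89 and it has 178. Simulated power with 31 per group and uncorrelated outcomes (1,500 runs per setting):

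| Contrasts | λ = 12.6 | λ = 18.9 | λ = 25.1 |
|---|---|---|---|
| 2 (sway area alone) | 0.78–0.81 | 0.95 | 0.98–0.99 |
| 16 | 0.32–0.33 | 0.51 | 0.68 |
| 32 | 0.20–0.21 | 0.31 | 0.42 |
| 88 | 0.05–0.06 | 0.07 | 0.06–0.07 |

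The middle column is calibrated so that sway area alone has about the planned power.

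**6. Power with correlation and other outcomes moving.** These runs use a common outcome correlation ρ from 0 to 0.7 and 600 runs per setting.
- *44 outcomes, λ = 18.9:* close to 5–8% if only sway area moves, and up to about 21–22% if the others move half as much and are uncorrelated. The largest effect (λ = 25.1) raised that last case to 27%. If all 44 move equally, power is 48% when uncorrelated but only 7–9% at ρ = 0.3 to 0.7 (λ = 18.9).
- *8 static outcomes, λ = 18.9, ρ = 0 / 0.3 / 0.5 / 0.7:* sway area only 54 / 67 / 82 / 99%; others half as much 97 / 58 / 51 / 60%; all equally 100 / 97 / 82 / 70%.
- *8 static outcomes, λ from 12.6 to 25.1:* the range is about 34% to nearly 100%.

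**The case against.** The best defence is that section 2.4 does not say all outcomes enter one model. Outcomes are tiered as primary, secondary and tertiary and grouped by domain in Table 2, so a MANOVA per domain or per condition fits the sentence and can be computed. The Bonferroni comparisons could also be made variable by variable, leaving sway area open to inspection. The Discussion expects static and dynamic balance to improve together, which can favour a multivariate test. The exact list of variables may sit in a fuller document.

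Most of this stands as a limit on the point. It does not restore the planned power: the domain-level test may be strong or weak for sway area, and the article gives no correlations to settle which. Post-hoc comparisons follow the main test and do not replace it. The objection that detail is merely left out also falls short, because the article does state a method and that method does not match the sample-size basis.

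A reader might infer three stronger things that the article does not support:
- *That the MANOVA cannot be computed at all.* At one value per listed variable, 88 is below 90. The singular cases need a fuller count or a real dependency.
- *That Table 2 contains exact duplicates.* No variable is listed twice. The stride identity requires the same strides, and the gait section describes more than one instrument without saying which supplies each time. Likewise, mean velocity equals total displacement divided by 30 s only if displacement means path length, which is undefined.
- *That the trial is underpowered for sway area.* The calculations show a weak test for that outcome. They do not show too few participants for a direct analysis of it.

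**Conclusion.** The point holds in a bounded form: the main-aim test as worded does not deliver the power on which the trial was sized.
- **One joint model:** 88 contrasts on 90 error df is barely computable, with power of about 6 to 22% when the other outcomes stay still or move half as much. With the static variables in all eight conditions (128 or 200 contrasts) no multivariate test exists.
- **One MANOVA per domain:** computable, but power for an effect on sway area runs from about 34% to nearly 100%.
- **Gait variables:** singular if stride, stance and swing times come from the same strides.

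These figures assume three groups of 31, three visits, a common correlation between outcomes, and noncentralities that give sway area alone about 78 to 99% power. None of the correlations is in the article.

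**What to change.** In section 2.4, replace the MANOVA as the main analysis with a univariate time-by-group repeated-measures (mixed) model of CoP sway area. Analyse each other outcome in its own model. If a multivariate summary is wanted, limit it to a few named, non-redundant variables (for example, stance and swing time without stride time) and label it supportive.

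This changes wording only, with no extra data or participants. What is lost is an omnibus statement across all outcomes, which neither stated aim requires.

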Balance alterations in PD are usually assessed in a single task. The most common tests are based on static and dynamic balance, where the patient controls the CoP in a static position (e.g., standing) (Negrini et al., 2017; Giardini et al., 2018; Soke et al., 2019) or during motion in direction to the different LoS (Kara et al., 2012; Carpinella et al., 2017; Soke et al., 2019). To this assessment methodology, it is common to add the blockade of the different systems that participate in balance regulation, either by closing the eyes or placing foam under the feet. Similarly, standard balance physiotherapy is carried out in isolated environments with exercises focused on single tasks or similar scenarios to those of the evaluation (Giardini et al., 2018). Conversely, daily activities are developed in highly challenging environments, which have been addressed in previous publications with Wii balance games (Yen et al., 2011; Zalecki et al., 2013; Carpinella et al., 2017; Negrini et al., 2017; Feng et al., 2019; Yuan et al., 2020), dual-task exercises within daily activities (Conradsson et al., 2015; Wong-Yu and Mak, 2015a, 2015b; Atterbury and Welman, 2017; Perumal et al., 2017; Santos et al., 2017; Wallén et al., 2018; Leavy et al., 2020), and single daily activities training (Smania et al., 2010; Kara et al., 2012b) including postural transferences (Millage et al., 2017; Soke et al., 2019). Although functional balance training (FBT) is included in the latest protocols, which consists of daily activities with feasible settings for older adults with PD, there are several methodological issues that have not yet been considered. One of these is the assessment methodology of the previous studies and the objectivity of the measurements, using in most cases, scales, and clinical tests only (Conradsson et al., 2015; Wong-Yu and Mak, 2015a,b; Atterbury and Welman, 2017; Perumal et al., 2017; Santos et al., 2017; Wallén et al., 2018; Leavy et al., 2020) instead of integrating biomechanical parameters of balance in different measurement conditions with a follow-up period after finishing the studied intervention (Kara et al., 2012b; Conradsson et al., 2015; Atterbury and Welman, 2017; Perumal et al., 2017; Santos et al., 2017; Soke et al., 2019; Leavy et al., 2020). Furthermore, the authors who inform significant improvement in balance biomechanics (Kara et al., 2012; Santos et al., 2017; Soke et al., 2019) do so in patients with normal cognition status and use habitual locations like a physiotherapy gym or hospital facilities. To respond to the challenges that emerged since the COVID-19 pandemic, such as the demand for rehabilitation programs that can be followed from home, the effect of domiciliary FBT and the long-term impact with adequate follow-up need still be determined, as well as the effects in people with PD in advanced stages where cognition is altered. For the foregoing, the aims of this study are (1) to quantify the effects achieved by domiciliary FBT on the biomechanics of balance, gait, perception of quality of life, cognitive and mental performance, and severity of PD in participants with and without cognitive impairment and (2) to compare them with the effects of a passive-control period and a conventional face-to-face physiotherapy program for PD. We hypothesized that balance home training based on functional exercises has a greater effect than the traditional physiotherapy group. If this hypothesis is confirmed, it will open the possibility of new rehabilitation strategies according to changes in post-pandemic therapeutic approaches, reducing morbidity, and saving costs to the healthcare system.

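### Post-hoc Bonferroni with an unnamed family is valid but inefficient: Holm on the two contrasts of aim 2 gives each about 2 to 17 points more power

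*Protocol article*

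**What the plan says.** All references are to the protocol article.

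- **Data collection, management, and statistical analysis.** The main analysis is a two-factor mixed MANOVA with assessment time within subjects and group between subjects. For what follows it, "The Bonferroni adjustment was used for" post-hoc comparisons, with significance declared below 0.05. The section states generally that analyses "used a level of significance of 0.05". It does not list or count the comparisons that share the correction.
- **Introduction, aim 2.** After quantifying the effects of home training, the aim is "to compare them with the effects of a passive-control period and a conventional face-to-face physiotherapy program for PD". That is two between-group questions: EG-PCG and EG-ACG. The one stated hypothesis is that home training does better than the traditional group programme, which is EG-ACG.
- **Sample size and recruitment.** The calculation targets a change in sway area and "differences between the groups (EG, PCG, ACG"). Its inputs are an effect size f of 0.15, a two-sided 5% level and 95% power. Its result is that "93 people diagnosed with PD will be recruited".
- **Abstract, Study design, and Assignment of interventions.** Two-thirds of participants are randomised 1:1 to EG or PCG and later cross over. The remaining third (ACG) already attend group physiotherapy and are not randomised.

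**The concern.** The multiplicity rule and the aims do not line up. Pairwise post-hoc testing of three groups gives three comparisons, so each is tested at 0.0167. The PCG-ACG comparison takes a third of the error rate, although neither the aims nor the hypothesis asks for it. The two contrasts that matter, the randomised EG-PCG and the hypothesis-bearing EG-ACG, are then tested more strictly than a 5% family-wise error requires.

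The choice of plain Bonferroni adds to the loss. On the same family, Holm controls the same error rate under the same conditions and rejects everything that Bonferroni rejects. At stake is a higher chance that a real effect on either aim-2 contrast is reported as non-significant.

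**Working it through.** **1. The plan's own figure.** For a repeated-measures within-between interaction F test in the G*Power form, λ = f²·N·m/(1−ρ), df1 = (g−1)(m−1) and df2 = (N−g)(m−1). From the protocol, f = 0.15, g = 3 and α = 0.05. The number of measurements m and their correlation ρ are not stated.

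- Assuming m = 6 (three assessments in each of two phases) and ρ = 0.5: λ = 0.0225 × 93 × 6 / 0.5 = 25.11, df 10 and 450, power 95.2%. N = 90 gives 94.4%. So 93 is reproduced.
- Assuming m = 3 and ρ = 0.5, the required N is 141. To get 93 with m = 3, ρ must be about 0.68.

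The planned 95% power belongs to this F test. It does not carry over to a pairwise contrast.

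**2. Model for the contrasts.** 93/3 = 31 per group, parallel change scores, pooled error df = 93 − 3 = 90. With d the difference in SDs of change, the noncentrality is d·√(31/2) = 3.937·d. For d = 0.72, chosen because it gives 80% power unadjusted, this is 2.835.

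| Two-sided level | Critical t (df 90) | Power at d = 0.72 |
|---|---|---|
| 0.05, unadjusted | 1.987 | 80% |
| 0.025, Bonferroni over two | 2.280 | 71% |
| 0.0167, Bonferroni over three | 2.440 | 65% |

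**3. Holm on EG-PCG and EG-ACG.** The smaller p-value is tested at 0.025. If it is rejected, the other is tested at 0.05. Power was simulated with the EG mean shared between the two contrasts.

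| d for EG-PCG, EG-ACG | Bonferroni over three pairs | Holm on two |
|---|---|---|
| 0.72, 0.72 | 65%, 65% | 76%, 76% |
| 0.72, 0.36 | 65%, 16% | 72%, 28% |
| 0.80, 0.50 | 76%, 33% | 82%, 48% |

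**4. Range, tied to f = 0.15.** Assume three assessments with the effect present at one of them, and EG alone differing. Then f = (2/9)·δ, so δ = 0.15/(2/9) = 0.675 and d = δ/√(2(1−ρ)).

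- EG alone differs, ρ = 0.5 (d = 0.675): each contrast 58.7% to 70.3%, +11.6. At ρ = 0.68 (d = 0.844): 80.9% to 88.9%, +8.0.
- ACG midway between EG and PCG, ρ from 0.5 to 0.68: EG-ACG gains 13.0 to 16.6 points (18.8% to 31.8% at ρ = 0.5). EG-PCG gains only 5.6 to 2.4.
- ACG as good as EG: EG-PCG gains 6.1 to 4.2.

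Across these patterns the gain per contrast is about 2 to 17 points.

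**5. If only two contrasts were meant.** At d = 0.72 for both, Bonferroni over two gives 71% and Holm 76%, a gain of about 5 points.

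**6. Error rate.** With no effect anywhere, the simulated family-wise error is 4.6% for Holm on two contrasts and 4.4% for Bonferroni on three pairs.

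**The case against.** **The family is not written down.** The model also has a three-level time factor, and aim 1 concerns the programme's own effects, so the post-hoc comparisons could be time pairs within group. A condensed article may leave such detail to a fuller document. This stands as a limit: a reader might infer that the protocol prescribes three group pairs at 0.0167, but the text does not say so. The point survives because the article itself chooses Bonferroni, and Holm gains under a two-contrast family as well.

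**Bonferroni is not a mistake.** This is correct. It controls the family-wise error, and nothing in the section is invalid on this point.

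**The size depends on assumptions.** A reader might take a gain of 11 to 15 points as typical. The documents do not support that, because they give no pairwise effect, SD or correlation. EG-PCG gains only about 6 or 7 points in the two unequal-effect rows of the table. For equal effects with 95% unadjusted power, three-pair Bonferroni costs 6.7 points and Holm recovers 5.7. The loss against unadjusted testing (14.7 points at 80% power) must also be kept apart from what Holm recovers (11.0).

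**The model is parallel, but EG and PCG cross over.** Using both periods would raise EG-PCG power and shrink the gain there.

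**PCG-ACG has some use.** It can help to interpret a null EG-ACG result, and the sample-size text refers to differences among all three groups. It would be wrong to call the change free, because the formal test of that pair is given up.

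**Conclusion.** The point holds as a cheap improvement in efficiency. The protocol applies Bonferroni to a family that it does not name. On the natural reading, that family includes a comparison that no aim or hypothesis asks for. Restricting it to EG-PCG and EG-ACG and using Holm keeps the family-wise error at or below 5%. It never lowers power for either contrast and needs no more participants.

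The gain is about 2 to 17 points per contrast. It is largest for EG-ACG when the conventional programme has an intermediate effect, and smallest for EG-PCG when that effect is large. These figures assume 31 analysed per group, parallel change scores, effect sizes that the protocol does not state, and a three-pair family as the starting point. The direction of the benefit does not depend on the effect sizes.

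The change does not address multiplicity across other outcomes and times, nor the fact that EG-ACG is a non-randomised comparison.

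**What to change.** In the statistical analysis section, replace the general post-hoc Bonferroni statement, for the primary outcome, with a rule of this kind:

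- Pre-specify one time point and one sway-area measure. The protocol has two post-baseline assessments (T1, T2) and eight static test conditions (four Romberg, four functional), and the 5% holds only once a single choice is fixed.
- Test two planned contrasts of change, EG-PCG and EG-ACG, by Holm at an overall two-sided 5%.
- Report PCG-ACG descriptively with a confidence interval.

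The change should be made before outcome data are examined by group.

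**Cost.** It takes a few lines of wording. Holm on two p-values can be done by hand from the software output, and no participants are added. There would be no formal claim on PCG-ACG, and Holm does not supply matching simultaneous confidence intervals.
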